**4.2 Progression Criteria**

A set of eight provisional progression criteria for the MAPSS programme have been established to determine whether a full RCT is warranted, and will be further developed in collaboration with the independent Trial Steering Committee (TSC; see Table 1). All progression criteria will need to be met for the MAPSS programme to be seen as acceptable and feasible, and to progress to a full efficacy trial.

*Table 1. Traffic light feasibility progression criteria*

| **Progression Criteria** | **Red**  **(stop)** | **Amber**  **(discuss and amend)** | **Green**  **(go)** |
| --- | --- | --- | --- |
| School recruitment (targeting n=6) | 1-2 schools recruited | 3-4 schools recruited | 6 schools recruited |
| Pupil participant recruitment (targeting n~810) | <20% of eligible pupils | 20-74% of eligible pupils | ≥75% of eligible pupils |
| School staff training recruitment | ≤2 teachers per school | 3-6 teachers per school | ≥6 teachers per school |
| Suicide Prevention workshop | <80% of scheduled workshops delivered | 80-99% of scheduled workshops delivered | 100% of scheduled workshops delivered |
| Pupils screening at high-risk of suicide | <5 pupils per school | 5-10 pupils per school | 10-15 pupils per school |
| Reframe IT-UK  Online CBT | <40% of eligible pupils engage with ≥75% of modules | 40-69% of eligible pupils engage with ≥75% of modules | ≥70% of eligible pupils engage with ≥75% of modules |
| Acceptability of intervention | <50% of pupils found MAPSS acceptable | 50-79% of pupils found MAPSS acceptable | ≥80% of pupils found MAPSS acceptable |
| Outcome data collected at baseline | Data collected from <50% of pupils | Data collected from 50-79% of pupils | Data collected from ≥80% of pupils |
| Follow-up outcome data attrition at T3 | >40% data attrition at T3 | 21-40% data attrition at T13 | ≤20% data attrition at T3 |

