Uptake and retention of participants in school-based intervention trials is a major issue that impacts the feasibility of future trials.^30^ This will be monitored through a mixed-methods evaluation encompassing quantitative and qualitative indicators. Quantitative indicators will include: a) comparisons of recruitment methods (for schools and then pupils into the study); b) successful data collection rates (low missing data); c) presence of floor/ceiling effects in collected data; d) whether responses on potential outcome measures remain static (or show ‘movement’) between baseline and follow-up; e) calculation of the precision of estimates of key parameters, which will inform a future trial. Qualitative indicators will include evaluation of the perceived mechanism of change and contextual factors impacting upon the effectiveness of the intervention for pupils and teachers. We will seek to interview participants who do not complete follow-up questionnaires to determine their reasons for not doing so and any factors that would improve completion rates. Factors that will determine stop/go procedures to a definitive trial will include: evidence that recruitment to a definitive study, using optimum recruitment pathways in one region, would be as follows: number of schools recruited at 9 months (6 excellent, 3-4 acceptable, 1-2 unacceptable), number of high-risk pupils recruited in the cluster-RCT per school (10-15 excellent, 5-10 acceptable, 0-5 unacceptable), and proportion of complete data collected (>80% acceptable). Retention will be judged by the following criteria: >80% completion excellent; 60-80% acceptable; below 60% unacceptable.

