**4.3 Planned intervention**

The training in schools for pupils, teachers, and parents will be funded by suicide prevention commissioners within the Local Authority (see Director of Public Health Letter).

1) A minimum of 6 staff from each school will receive training from Papyrus: **Suicide Prevention – Overview Tutorial (SP-OT)**, to ensure staff are equipped to manage any risk identified from the screening. SP-OT is delivered in a single session over 1.5 hours online. Papyrus will also provide an online information session, **Suicide Prevention - Awareness, Resource, Knowledge (SP-ARK),** along with support packs, for parents of all children in Year 10 at each participating school. #MyGPGuide; a guide for CYP with lived experience of self-harm and suicidality will be shared with schools and families.^31^

2) **Suicide prevention lesson** such as safeTALK, developed by LivingWorks Education,^32^ a suicide alertness training workshop suitable for anyone over the age of 14. The lesson comprises a single 3.5-hour face-to-face workshop, designed to help participants understand suicide warning signs in themselves and others, gain knowledge about sources of support, apply basic ‘TALK’ steps (Tell, Ask, Listen, and KeepSafe), and signpost others. Suicide prevention lessons will be delivered by trained Suicide Prevention Facilitators at Grassroots Suicide Prevention to classroom-sized groups of pupils (maximum 30 pupils per session with at least one teacher present).

3) The **screening** will take the form of self-report measures embedded into the questionnaires at each timepoint. Researchers will inform each school after each timepoint of any pupils who are assessed to be at risk. Pupils who report suicidal ideation within the past four weeks (Suicide Ideation Attributes Scale [SIDAS] score of 21 or higher)^33^ or any level of current suicidal ideation (single multiple-choice item) will be flagged by the research team and followed up by the school safeguarding lead.

4) **Reframe IT-UK** has been adapted from the Reframe-IT intervention developed in Australia.^17,27^ It comprises eight 20-minute online self-guided CBT modules, following the stories of two young people who make video diaries about their day-to-day life and their experience of feeling suicidal. There is also a message board through which the participants can communicate with a moderator, a mood diary, and signposting information.

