***Qualitative Process Evaluation***

We will conduct longitudinal case studies of the 4 schools randomised to receive MAPSS. The case studies will explore inter-related issues of 1) social validity of MAPSS and 2) *how* MAPSS was implemented and *why* it was implemented in this way. In terms of social validity, we will utilise Wolf’s framework,^34^ focusing on key tenets of acceptability, feasibility, and utility (e.g., does the intervention meet schools’ perceived needs? How well received is the intervention among staff and pupils? Can the intervention be delivered successfully?). Here we will draw upon relevant studies of school-based interventions (e.g., Kendal, et al)^35^ and adapt existing rubrics from the implementation literature (e.g., Bird et al)^36^ to inform our data generation.

In terms of how MAPSS was implemented, we will focus on the following dimensions: fidelity (e.g., to what extent teachers adhered to MAPSS guidance), dosage (e.g., how much of MAPSS pupils accessed), quality (e.g., how well MAPSS was delivered), participant responsiveness (e.g., the extent to which pupils engaged), reach (e.g., the rate and scope of participation), programme differentiation (e.g., to what extent MAPSS can be distinguished from other, existing mental health programmes), and adaptations (e.g., the nature and extent of changes made during implementation). We will also explore a range of factors that may have affected implementation at the different domains/levels consistently: preplanning and foundations (e.g. buy-in), implementation support system (e.g. ongoing external support), implementation environment (e.g. time constraints), implementer factors (e.g. experiences, skills and confidence in delivery), and programme characteristics (e.g. flexibility).^36-38^

***Methods for Sharing Study Progress and Findings with Participants and Payments, Rewards and Recognition for Participants***

Each participating school will be invited to nominate a minimum of 6 key staff members to complete SP-OT training delivered by Papyrus, to increase staff capacity to enact safety protocols, and to act as an incentive for schools to participate. To ensure safety and appropriate support in the event of pupils being flagged as at-risk, schools who do not engage with the SP-OT training will be unable to progress through the trial.

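### Progression bands in Table 1 leave gaps and overlaps: five schools has no verdict, six trained staff has two, and the high-risk pupil row has both faults

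*Protocol*

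**What the plan says.** Section 4.2 sets out traffic-light criteria in Table 1 and gives the decision rule: "All progression criteria will need to be met for the MAPSS programme to be seen as acceptable and feasible". It calls the criteria provisional and says they "will be further developed in collaboration with the independent Trial Steering Committee".

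Three rows matter here, each in the order Red, Amber, Green:

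- School recruitment, target six: "1-2 schools recruited | 3-4 schools recruited | 6 schools recruited".
- Staff training: "≤2 teachers per school | 3-6 teachers per school | ≥6 teachers per school".
- Pupils screening at high risk, per school: fewer than 5, then 5-10, then 10-15.

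Section 4.1 states stop/go factors for two of these. For schools it gives "number of schools recruited at 9 months (6 excellent, 3-4 acceptable, 1-2 unacceptable". For high-risk pupils recruited per school it gives 10-15 as excellent, 5-10 as acceptable and 0-5 as unacceptable.

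The planned staff number appears twice. Section 4.3 says "A minimum of 6 staff from each school will receive training from Papyrus", and Section 4.7 says "Each participating school will be invited to nominate a minimum of 6 key staff members to complete SP-OT training".

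**The concern.** A traffic-light table works as a pre-specified rule only if each possible result falls in exactly one band. Here one result just below the recruitment target has no band, and the planned minimum for staff training has two. The high-risk pupil row overlaps at 10 and stops at 15, close to the number the Protocol expects.

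The third primary aim is to judge the feasibility of a definitive cluster trial, and Table 1 is the tool for that judgement. Because all criteria must be met, one row without a single verdict can leave the overall decision open. If the boundaries are settled only after the counts are known, the choice of colour can be influenced by the result, which is what setting the bands in advance is meant to prevent.

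**Working it through.** No sample-size or power figure is involved. The check takes each whole-number result and reads off the bands that contain it.

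**Schools** (Table 1; Section 4.1 uses the same cut-points)

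| Schools | Band(s) as written |
|---|---|
| 0 | none |
| 1-2 | Red |
| 3-4 | Amber |
| 5 | none |
| 6 | Green |
| 7 | none |

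Five is missing in both places, so this is not a slip in one table cell. Seven or more matters because Section 11 allows recruitment sites to be added if recruitment is slow.

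**Trained staff per school** (Table 1)

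| Staff | Band(s) as written |
|---|---|
| 0-2 | Red |
| 3-5 | Amber |
| 6 | Amber and Green |
| 7 or more | Green |

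The only double-scored value is six, which is the planned minimum in Sections 4.3 and 4.7.

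**High-risk pupils per school**

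| Pupils | Table 1 | Section 4.1 |
|---|---|---|
| 0-4 | Red | unacceptable |
| 5 | Amber | unacceptable and acceptable |
| 6-9 | Amber | acceptable |
| 10 | Amber and Green | acceptable and excellent |
| 11-15 | Green | excellent |
| 16 or more | none | none |

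Expected number: Section 4.6 gives about 54 at-risk pupils in four intervention schools and about 27 in two control schools. 54/4 = 13.5 and 27/2 = 13.5 per school. The 10% at-risk rate in Section 4.8 agrees: 810/6 = 135 pupils per school, and 0.10 × 135 = 13.5. The expected value therefore lies 15 − 13.5 = 1.5 pupils below the point where the bands stop. At the same 10% rate, a school with 160 pupils in the year group would give 16 and have no band.

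**Meaning of per school.** The phrase appears in the staff and high-risk rows, not in the school-recruitment row. The Protocol does not say whether it means every school or the average. This affects the cut-points. If three schools train 2 staff and three train 3, the average is (3×2 + 3×3)/6 = 2.5, which lies between Red (≤2) and Amber (from 3) and has no band.

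**Bands after correction.** With schools at 0-2, 3-5 and ≥6, each count from 0 upward falls in exactly one band. The same holds for staff at ≤2, 3-5 and ≥6.

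**The case against.** The strongest case is that the gaps barely affect the decision. Green for schools is six and Red ends at two, so five is Amber by elimination. If a criterion is met only when Green, five fails just as four does; if it is met when not Red, five passes just as four does. For staff, the double score changes the go decision only if met means Green, and the planned minimum of six suggests Green was intended, with Amber 3-6 a slip for 3-5. The criteria are also provisional.

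Much of this stands as a limit on severity. It does not remove the fault. The elimination argument is the reader's, not the Protocol's: no section assigns five schools to a band or breaks the tie at six staff. Section 4.2 does not say whether met means Green or merely not Red, so the consequence at six staff stays open. The Protocol gives no date by which the bands must be final and does not mark these boundaries for revision.

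Three stronger readings are tempting and are not supported:

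- A reader might infer that five schools and six staff are the likeliest near-plan results and attach a probability to five of six. The documents give no recruitment probability, and treating six schools as fixed and independent does not fit Section 11, which says many further sites exist and can be added. Six staff is a floor, and a school training seven or more is clearly Green.
- A reader might say that six staff cannot be classified. It is classified twice, which is a different fault, although again no single verdict follows.
- A reader might take the staff criterion to be scored on the lowest school. That would be a new and stricter rule. The Protocol does not imply it, and Sections 4.4 and 4.7 already bar schools that do not engage with the staff training from progressing.

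**Conclusion.** Wrong as written. Five schools receives no verdict in Table 1 or Section 4.1. Six trained staff, the planned minimum, receives two. Ten high-risk pupils per school receives two in both places, five receives two in Section 4.1, and more than 15 receives none, against an expected 13.5.

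This follows from the bands alone and needs no assumption about how likely each result is. The effect on the final decision is conditional. For schools it is small if five is read as Amber. For staff, and for high-risk pupils at 10, it matters if a criterion is met only when Green. The provisional status lowers the seriousness, but the bands form part of the go/no-go rule and should be put right before any results are seen.

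**What to change.** - **Schools**, in Table 1 and Section 4.1: Red 0-2, Amber 3-5, Green ≥6, with the Section 4.1 labels matched to these. The open upper end covers any added sites.
- **Staff training**, in Table 1: Red ≤2, Amber 3-5, Green ≥6.
- **High-risk pupils**, in Table 1 and Section 4.1: make the bands non-overlapping at 5 and 10, state a verdict for more than 15, and use the same cut-points in both places. Which band holds each boundary value is for the sponsor and the Trial Steering Committee to decide.
- **Per school**: the sponsor and the Trial Steering Committee should state in advance whether it means every school or the average. If the average is chosen, the cut-points must also cover fractional values such as 2.5, or 5.5 under the corrected staff bands.

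The cost is wording only: no extra data, schools or analysis. The changes should be made before recruitment and training counts are reviewed.

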**4.12 Data and Statistical Analysis**

***Quantitative Data Analysis***

Changes in primary and secondary outcomes over time will be assessed for pupils clustered within schools and the treatment group included as a fixed factor. The analysis will adopt the intention-to-treat approach. As a secondary analysis, compliance (as measured by the number of modules completed) and other potential covariates (e.g., gender) will be accounted for. If the amount of missing data is non-trivial, multiple imputation will be used. We will follow the recently published extension to CONSORT^42^ when reporting the results of this feasibility trial. We will calculate and present in a CONSORT flow chart:

- - 1. The proportion of young people with suicide ideation consenting to the study;
    2. The proportion completing baseline assessment and entering the randomised phase;
    3. The number of online modules used and the proportion completing all sessions;
    4. The proportion completing follow-up assessments at 12-weeks and one-year post-randomisation.

As this is a feasibility study, no formal hypothesis testing will take place. Quantitative data will be reported using summary statistics and 95% confidence intervals. We will compare the continuous scores on the SIDAS outcome measure graphically to assess between group trends. The SD of the primary outcome will inform the sample size calculation for the large-scale RCT.

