**4.16 Socioeconomic Position and Inequalities**

As part of the scoping study conducted to inform the adaptation of the intervention for the UK, we used the health inequalities assessment tool (HIAT – FOR-EQUITY; forequity.uk)^59^ to ensure that we addressed inequalities. The HIAT aims to support researchers (and stakeholders) to integrate an intersectional equity lens into research and consider how people with lived experience and policy or practice expertise can help in this process. We have also since completed the NIHR Equality Impact Assessment. From the outset, we ensured that we involved parents from different cultural backgrounds and CYP from schools in communities with different levels of deprivation. We do not anticipate pupils being excluded from taking part in the MAPSS programme as it will be commissioned by Local Authorities as a school-based workshop. However, parents/carers will have received notification about the workshop and will be able to opt their children out of attending. We will record demographic data for pupils who are not consented to attend the suicide prevention lesson or those not consented to take up the Reframe IT-UK intervention, to review the reasons of why this may be. We will be adopting purposeful maximum variation sampling to recruit schools and have dedicated time in the study to ensure we recruit a diverse sample (see section 4.6 above further details). We have also adapted the materials as part of the Reframe IT-UK intervention, which includes video diaries recorded by young people (actors). We have ensured that actors and their stories are diverse and reflect the socio-demographic characteristics of UK schools, and we have worked with young people to develop these. So far, we have not needed to translate study materials for Year 10 pupils in mainstream secondary schools in the UK. However, if we do encounter such issues, we will record and report these findings to inform the design of future trials. Findings from our scoping study suggested that some elements of MAPSS were not accessible for neurodivergent pupils, and recommended adaptations were implemented for the pilot study (e.g., Reframe IT-UK is now completed with a pastoral member of staff, the workshop has more breaks). However, we have been monitoring this throughout the pilot study, and will make any further adaptations (if necessary) for the feasibility trial.

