**8. Ethics**

Ethical approval will be obtained from LJMU prior to study commencement. The study will always be undertaken in compliance with the research protocol. All participants will be given a participant information sheet and consent form prior to taking part in interviews. Personal data will be documented in a password protected and encrypted computer. No identifiable patient data will be extracted.

As delivery of the intervention is being arranged by local Public Health bodies, consent will only be sought for completion of the measures. While opt-in gatekeeper consent will be sought from the participating schools, opt-out consent will be sought from parents of YP. Findings from both our scoping and pilot study consistently showed that opt-out consent is feasible and desirable for this project. Given the potentially sensitive nature of the measures, parents/carers will be informed of the project on two separate occasions (via the schools’ usual communication channels), to help ensure information is not missed. Schools will also be asked to advise parents/carers of the date scheduled for survey completion, so they are aware. All parents will be provided with detailed information sheets (alternative format/easy-read will also be developed), outlining the importance of the study, any risk of harm (and procedures put in place to reduce this), and will be provided with detailed signposting. Parents will be able to view the items in the survey if requested and attend an online information session about suicide prevention in young people. Parents and carers who are Co-Is and PPI advisory members will be consulted to ensure 1) improved attendance at the parent information sessions and 2) parents/carers are effectively informed about any young people who may be at risk of suicide and equipped with appropriate resources and support.

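### The high-risk progression criterion counts recruited pupils in section 4.1 but screen-positive pupils in Table 1, and the Reframe IT-UK row that should capture uptake has no fixed denominator

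*Protocol*

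**What the plan says.** Section 4.1 lists among the stop/go factors the "number of high-risk pupils recruited in the cluster-RCT per school (10-15 excellent, 5-10 acceptable, 0-5 unacceptable"). Table 1 in section 4.2 has a row headed "Pupils screening at high-risk of suicide", with Red, Amber and Green set at "<5 pupils per school | 5-10 pupils per school | 10-15 pupils per school".

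The next row of Table 1 concerns Reframe IT-UK. It is Red at "<40% of eligible pupils engage with ≥75% of modules" and Green at "≥70% of eligible pupils engage with ≥75% of modules". Section 4.2 requires every criterion to be met, and calls the set provisional and open to development with the Trial Steering Committee.

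Four sections bear on who is eligible:

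- Section 4.3 flags pupils with a SIDAS score of 21 or higher, or any current ideation.
- Section 4.6 offers Reframe IT-UK at SIDAS 21 or above, or past ideation.
- Section 4.7 has eligibility settled with the school after a pupil is flagged.
- Section 4.8 expects 10% to screen in the at-risk range and treats those pupils as eligible.

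On consent, section 8 says that "consent will only be sought for completion of the measures" and also describes Reframe IT-UK as voluntary. Section 4.16 plans to record demographics of "those not consented to take up the Reframe IT-UK intervention". The first CONSORT item in section 4.12 is "The proportion of young people with suicide ideation consenting to the study".

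**The concern.** Two stop/go rules use almost the same cut-points for what read as different quantities. A count of pupils who screen positive reflects prevalence, school size and survey participation. It does not show whether at-risk pupils will take up the indicated component, which is a main recruitment uncertainty for a definitive trial; section 4.1 itself names uptake as a major threat to future trials. If the two rules diverge on the same data, the decision to progress depends on which section is read.

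The Reframe IT-UK row could supply the missing information, but only if its denominator is settled. The CONSORT item that seems meant to show consent among pupils with ideation may have no observable denominator.

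**Working it through.** **Inputs.** About 810 pupils, 6 schools, 4 intervention and 2 control, about 54 and 27 at-risk pupils (4.6); 10% at risk (4.8); bands from 4.1 and Table 1.

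**1. The plan's own figures.** 810 / 6 = 135 per school. Intervention: 135 x 4 x 0.10 = 54. Control: 135 x 2 x 0.10 = 27. Both reproduce. Per school: 135 x 0.10 = 13.5.

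**2. The screening row.** 13.5 lies in the Green band of 10-15 before any pupil is offered Reframe IT-UK. Under a simple binomial (n = 135, p = 0.10, clustering ignored), P(at least 10) = 0.88 and P(10 to 15) = 0.60. The difference between the two is the chance of more than 15, which falls in no band.

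**3. The 4.1 rule, if recruited means joining Reframe IT-UK.** Excellent needs 10 / 13.5 = 74% uptake. Below 5 / 13.5 = 37% the school is unacceptable. At 50% uptake there are 0.5 x 13.5 = 6.75 recruits: acceptable in 4.1, while the screening row stays Green.

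**4. The bands.** The lowest is 0-5 in 4.1 and below 5 in Table 1. Exactly 5 pupils is therefore both unacceptable and acceptable in 4.1, and Amber in Table 1. In both places 10 falls in two bands.

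**5. The Reframe IT-UK row, if eligible means all screen-positive pupils.**

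| Screen-positive per school | Engaged pupils needed for Green (70%) | Largest whole number still Red (<40%) |
|---|---|---|
| 10 | 7 | 3 |
| 13.5 | 9.45, so 10 | 5 |
| 15 | 10.5, so 11 | 5 |

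Zero joiners gives 0%, which is Red. At 50% uptake, engagement cannot exceed 50%, which is Amber at best.

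**6. The same row, if the school narrows eligibility.** As an illustration, take 14 flagged, 3 judged eligible and all 3 engaging. The screening row is Green (14) and the Reframe IT-UK row is Green (3/3 = 100%), with three participants. Three joiners would be unacceptable on the joining reading of 4.1.

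**7. Uptake and adherence are mixed.** Half of eligible pupils joining and all adhering gives 0.5 x 1.0 = 50%. All joining and half adhering gives 1.0 x 0.5 = 50%. Both are Amber, yet they call for different remedies.

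**8. The CONSORT item.** Pupils agree by a tick-box at the start of the survey (section 8), and the screen is inside that survey (4.3). Ideation is thus seen only in pupils who have already agreed. If the item means study consent, pupils with ideation who declined are never observed and the proportion cannot be formed.

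**The case against.** A reader might infer that Table 1 as a whole could be Green with no at-risk pupils joining Reframe IT-UK. The documents do not support that. The Reframe IT-UK row would be Red at zero joiners when eligible means screen-positive, as section 4.8 has it, and all criteria must be met. Only the screening row is uninformative about uptake. Passing with very few participants requires a narrow reading of eligible.

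Recruited in the trial also need not mean joining Reframe IT-UK. The criterion is per school, control schools are in the trial but are not offered the programme, and research consent covers only the measures. A surveyed pupil who screens positive may already count as recruited, so 4.1 and Table 1 may intend the same count. This stands as a possible reading, and it makes the 74% and 37% figures conditional. On that reading, though, no progression criterion directly counts at-risk pupils who accept the indicated component.

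The screening count is not pure prevalence either. It falls with opt-outs and survey refusal: at 50% participation, 13.5 becomes 6.75, which is Amber.

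The sections on consent can coexist. Section 8 limits research consent because public health bodies arrange delivery, and take-up of an offered service can still be voluntary. The wording in 4.16 is loose rather than a flat contradiction, and 4.16 already plans part of the recording needed. The CONSORT item would be computable if it meant agreement to the indicated stage among flagged pupils, but it refers to the study.

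**Conclusion.** The point holds in this form. Section 4.1 and Table 1 define the high-risk criterion differently on nearly the same bands. At the planned 13.5 per school the Table 1 row is Green without information on uptake, assuming 10% prevalence and the full 810 surveyed. On the joining reading, the 4.1 grade for that school runs from unacceptable (below about 37% uptake) to excellent (about 74% or more) while the Table 1 row does not move.

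The Reframe IT-UK row covers part of the gap, but it combines uptake with adherence, and its denominator differs between sections 4.3, 4.6, 4.7 and 4.8. The number of engaged pupils needed for Green is therefore not fixed: it is 7 to 11 per school across the Green screening range if all screen-positive pupils are eligible, and could be as few as 3 in the illustration above.

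The first CONSORT item cannot be computed on its plain reading. This should be fixed, but it does not undermine the trial: the criteria are provisional and zero uptake would be caught on the section 4.8 definition.

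**What to change.** - Use one counted quantity in section 4.1 and Table 1, with bands that neither overlap nor leave gaps.
- Reconcile sections 4.3, 4.6, 4.7 and 4.8 on flagging and eligibility, and fix the denominator of the Reframe IT-UK row before data are seen. Which eligibility rule applies is for the investigators to settle.
- Report the number screening positive as a descriptive prevalence in both arms.
- In the intervention schools, report uptake (accepted / offered) separately from module adherence, extending the recording planned in 4.16.
- Replace the first CONSORT item with a chain that can be counted: on roll, not opted out, agreed and surveyed, screened at risk, offered Reframe IT-UK, accepted.
- Align 4.16 and section 8 on whether and how agreement to Reframe IT-UK is obtained.

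The cost is protocol wording and one offer/accept field per flagged pupil. The downside is that a criterion based on uptake may be harder to meet than a count of screen-positive pupils.
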